#### Community health outreach days

After the ninth intervention session, local organizations are mobilized to coordinate accessible community health events that aim to increase HIV-testing among families through promoting an overall focus on child health. They take place in several locations over a 4-week period and are targeted at both intervention and control villages. The events are structured in clusters of communities based on their geography. The community health outreach days provide a wide range of services which include nutrition assessments, vaccinations, HIV-testing and counseling, general health consultations, birth document registration, and delivery of information on child protection and community gardening. Project partners work with a number of local partners to run these events: Baylor College of Medicine Children’s Foundation Lesotho, the Child and Gender Protection Unit, the Ministry of Health’s District Health Management Team, the Food and Nutrition Coordinating Office, the Ministry of Agriculture and Food Security, the National Identity Civil Registry, and a local nongovernmental organization called Touching Tiny Lives.

### Control condition

The control villages in the study do not receive the group-based integrated intervention, but they are invited to take part in community health outreach days that take place in an accessible venue near to their homes and provide access to a range of services, including HIV-testing and counseling and nutrition assessments. They have access to standard health services available in Lesotho, primarily delivered through primary health care services in the district. In addition, each control village has an informal paid preschool service available in their village.

### Participant recruitment

All children aged 1–5 years at the time of baseline assessment who are living in study villages are eligible for participation in the study, regardless of whether or not they attend the paid village preschool. They are enrolled together with their primary caregivers. Adult primary caregivers enrolled in the study are included if they are 18 years or older, serve as a primary caregiver for the child, live in the same house as the child at least four nights per week, and provide consent for themselves and their child to participate in the study including intervention and completing baseline, and immediate post test and 12-month follow-up assessments.

After agreement from the local chief and community leadership, trained recruiters go door-to-door in villages to identify children within the age range of the study. They collect basic demographic information on participants who agree in principle to take part. At a later stage, following a recruitment visit at which formal consent to participate in the trial is obtained, there is a further visit from a baseline data collector.

### Data collection

#### Data collector training

Data collector training consists of principles of research ethics, referral procedures, and management of difficult situations in the field. The data collector team members have learned how to complete the informed consent procedure with a focus on how to handle participants with low literacy levels, and how to administer the questionnaire including dealing with sensitive issues. In addition team members have been extensively trained on how to administer the child developmental assessments that are used in the study. This includes principles of child assessment, how to set up the assessment space, establishing rapport with young children, child seating and positioning, and how to minimize and manage distractions in the community setting.

#### Procedures

Table 2 shows the study schedule which follows the Standard Protocol Items: Recommendations for Interventional Trials (SPIRIT) guidelines.

**Table 2 Tab2:** Schedule of enrollment, interventions, and assessments following the Standard Protocol Items: Recommendations for Interventional Trials (SPIRIT) figure

	Allocation	Enrollment	Post allocation					Close-out
			Weeks 1–8	Weeks 6–18	Weeks 16–24	Weeks 21–25	Weeks 68–76	
Time point	0		Baseline	Group intervention	Post-intervention follow-up	Community health outreach day	12-month follow-up	18 months post intervention
Enrollment:		X	X					
Eligibility screen		X						
Informed consent			X	X	X		X	
Allocation	X							
Interventions:								
Intervention condition				X		X		
Control condition						X		
Assessments:								
Primary outcomes:								
HIV-testing rate			X		X		X	
Child language			X		X		X	
Child attention			X		X		X	
Secondary outcomes:			X		X		X	
Child cognitive development			X		X		X	
Child growth			X		X		X	
HIV treatment uptake			X		X		X	
HIV treatment adherence			X		X		X	
Child emotional and behavioral functioning			X		X		X	
Child executive functioning			X		X		X	
Parental discipline			X		X		X	
Parenting stress			X		X		X	
Parental sensitivity			X		X		X	
Caregiver mental health			X		X		X	
Alcohol use			X		X		X	
Mediators:			X		X		X	
Positive parenting			X		X		X	
Stimulation of child at home and preschool			X		X		X	
Moderators:								
Socioeconomic status			X		X		X	
Family structure/caregiver relationship			X		X		X	
Caregiver mental health			X		X		X	
Child gender		X						
Quality/fidelity of intervention received			X		X		X	

The study flowchart is included in Table 3. Data are collected at baseline and again at two follow-up points: 2 weeks post intervention and 12 months post intervention. Data collectors are blind to intervention group. They travel to the villages in teams and remain in each village over several days while data collection is underway. They first meet with potential participants and conduct the informed consent process before starting any research activities. All data collection takes place in rented houses within the villages which provide a quiet and private space for all interviews and assessments. Following data collection participants are provided with a small package of groceries for their time, consisting of soap, washing powder, breakfast bars, and juices.

**Table 3 Tab3:** Primary and secondary outcome measures

Outcome	Measure
Primary outcomes	
HIV-testing rate	Number of children who have tested for HIV in the past 3 months
Child language	MacArthur Communication Development Inventory (CDI)
	Peabody Picture Vocabulary Test (PPVT)
	Mullen Scales of Early Learning: Receptive Language Scale
Child attention	Early Childhood Vigilance Task (ECVT)
Secondary outcomes	
Child cognitive development	Mullen Scales of Early Learning: Visual Reception Scale
Child growth	*Z*-scores, based on WHO standards
HIV treatment uptake	Number of children initiating ART therapy after testing
HIV treatment adherence	ART adherence rates in children, defined as % adhering to ART within defined periods (3 days, 1 week, 1 month)
Child emotional and behavioral functioning	Child Behavior Checklist (selected subscales)
	Strengths and Difficulties Questionnaire
Child executive function	Inhibitory control task
	Attention shifting task
	Working memory task
Parental discipline	Discipline and Violence Questionnaire of Lansford and Deater-Deckard, developed from the Parent-Child Conflict Tactics Scale and the World-SAFE survey
Parenting stress	Parenting Stress Index (PSI)
Parental sensitivity	Directly observed book-sharing task rated with adapted version of the Murray Global Rating Scales
	Directly observed problem-solving task rated with adapted version of the Murray Global Rating Scales
Caregiver mental health	Patient Health Questionnaire-9 (PHQ-9)
	Generalized Anxiety Disorder-7 (GAD-7)
	Self-Reporting Questionnaire-20 (SRQ-20)
	Shona Symptom Questionnaire
Caregiver alcohol use	Alcohol Use Disorders Identification Test (AUDIT)

*ART* antiretroviral therapy, *WHO* World Health Organization

Data are collected by the data collectors on tablet computers, which instantly transmit participant responses to a server, thus minimising data-entry errors. Automated data collection methods have been shown to be especially effective in increasing participant willingness to disclose highly-stigmatizing activities or experiences [29]. With participant consent, caregiver interviews are audio-recorded and child assessments are videoed for quality control purposes. Data are checked in weekly batches to allow for constant data-quality monitoring. Tablets are password-protected and data transmitted from them are held on a password-protected central network server.

### Measures

Outcome data are collected through the use of (1) caregiver interviews, (2) direct child assessments, and (3) videoed caregiver-child interactions. Caregiver interviews and child assessments have been translated and back-translated (where applicable) into Sesotho [30]. The primary outcomes are:HIV-testing rate. This is calculated as the number of children who have tested for HIV in the previous 3 monthsChild language. This is measured using three standardized language measures: the MacArthur Communication Development Inventory [31], a parent-reported measure of early language which was used in the previous study of dialogic book-sharing in Khayelitsha, South Africa [25], the Peabody Picture Vocabulary Test [32], a measure of receptive vocabulary, adapted for use in Lesotho, and the Receptive Language Scale, a subtest of the Mullen Scales of Early Learning [33] which assesses a child’s ability to decode and respond to varying levels of verbal instructionChild attention (Early Childhood Vigilance Task) [34] is measured using a computer-based assessment of sustained attention during which the child is required to watch a screen where various animated stimuli disappear and reappear. This measure was also used in the previous study of dialogic book-sharing in South Africa

Secondary outcomes for child participants include HIV treatment uptake and adherence, cognitive development, executive function, emotional and behavioral functioning, and growth status. For caregivers, secondary outcomes include caregiver mental health and substance use, and parenting outcomes such as discipline, parenting stress, and parental sensitivity. All videoed interactions will be coded by reviewers who are blinded to group allocation. Primary and secondary outcome measures are detailed further in Table 3.

### Data quality control

Individual child assessments and caregiver interviews are videoed and audio-recorded, respectively, and a randomly selected subsample of each is reviewed by a team of data quality controllers. This includes listening to caregiver interviews to ensure that data collectors are not deviating from the prescribed sets of questions and answers, that they are making referrals when appropriate, and that they are treating research participants with respect during all study procedures. Child assessment videos are reviewed to ensure that data collectors are scoring items correctly and following the correct basal and ceiling rules for certain tests. The team receives feedback on an ongoing basis.

### Data analysis plans

Data analysis will be completed by a designated statistician/statistical team that is independent from study investigators. Baseline differences between intervention and control groups will be examined using independent *t* tests [35]. In addition to the primary and secondary outcomes, analysis of baseline differences will also include sociodemographic data such as age, gender, and household poverty.

Intervention efficacy will be evaluated by comparing child outcomes over 12 months between the intervention and control groups. Post-test scores for primary outcomes and secondary outcomes will be used as dependent variables. Parent/child age and gender, allocation group, and baseline scores will be included as covariates [36]. Analyses will also control for intervention site in order to account for variance in implementation among sites [37]. Scores will be compared using multilevel models, (i.e., hierarchical models or random effect models) which can account for clustering of repeated assessments within individuals and clustering of individuals within villages [38, 39]. If data are normally distributed we will fit linear models. If not, we will categorize outcome data and use longitudinal logistic regression to assess differences between intervention and control villages. Intervention effects will be examined using an intention-to-treat analysis [40]. Intention-to-treat considers all participants in an experiment regardless of whether they do or do not complete the program or evaluation [41].

Clustering will be taken into account in all analyses and multiple imputation methods will be used for missing individual outcome data [42]. We will also examine the effect of the intervention dose to assess the relationship between outcomes, phase of intervention, and the number of sessions attended and other process data relating to the implementation of the intervention.

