**Methods:**

We are conducting a cluster randomised controlled trial in Mokhotlong district, Lesotho, to evaluate a newly developed community-based intervention program to integrate HIV-testing and treatment services, ECCD, and nutrition education for caregivers with children aged 1–5 years living in rural villages. Caregivers and their children are randomly assigned by village to intervention or control condition. We select, train, and supervise community health workers recruited to implement the intervention, which consists of nine group-based sessions with caregivers and children over 12 weeks (eight weekly sessions, and a ninth top-up session 1 month later), followed by a locally hosted community health outreach day event. Group-based sessions focus on using early dialogic book-sharing to promote cognitive development and caregiver-child interaction, health-related messages, including motivation for HIV-testing and treatment uptake for young children, and locally appropriate nutrition education. All children aged 1–5 years and their primary caregivers living in study villages are eligible for participation. Caregivers and their children will be interviewed and assessed at baseline, after completion of the intervention, and 12 months post intervention.

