### Study setting

The study takes place in 34 villages in the Mokhotlong district in north-eastern Lesotho (see Fig. 1). Villages are very remote, with poor transport and road facilities, and severe weather conditions, especially in the winter months. The intervention is delivered in informal preschools in rural villages in the district. All children in the villages are included, regardless of whether or not they regularly attend the preschool. These informal preschools are run by local community members, often in their own homes, which are usually stone and mud houses without electricity or running water. Preschool staff have limited or no toys, books, or equipment, but are usually provided with support from the district Ministry of Education and Training in the form of monthly meetings and training workshops.

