### Neighborhood selection, matching and randomization

The selected clusters for the study were identified as villages where GROW had a resident community volunteer, and where there were informal preschool centers in operation. It was important to identify villages with an operational ECCD center, since the study makes use of these facilities to deliver the intervention to young children and their primary caregivers.

Prior to cluster randomization, all eligible villages were mapped in order to determine the approximate number of children aged 1–5 years per village, the characteristics of the communities, the number of preschool centers, and the available government and nongovernmental services. Mapping (and subsequent data collection) in some villages requires transport by donkey due to inaccessibility by vehicle. Trained field-workers conducted the mapping exercise in two stages. During the primary mapping exercise, field-workers collected information at village level, preschool center level, and health care level for all villages. During the secondary mapping exercise, field-workers returned to the two largest, the two mid-size, and the two smallest villages to identify the number of children aged 1–5 years in each household.

Based on the village mapping activity, 34 villages were matched into pairs based on various community, preschool and health service characteristics, and stratified by size and relative remoteness. In each pair, villages were then randomly assigned to the intervention group, where participants are allocated to the intervention or the control group using a free web-based randomization program [23]. Randomization was overseen by an external statistician and the procedure followed Consolidated Standards of Reporting Trials (CONSORT) guidelines [24]. The overall sample of villages was divided into two phases: phase 1 and phase 2, with phase 1 IC villages receiving the intervention first, followed by the roll-out of the intervention in phase 2 IC villages.

Researchers notified intervention and control village leadership, preschool staff, and community members about their allocation individually. All data collectors and data coders are blinded to group allocation in order to minimize assessment bias [23] and study participants are asked not to reveal their condition to data collectors at any point.

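### Control for an undefined intervention site is either collinear with allocation or redundant, and its stated purpose is a post-randomisation feature of one arm

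*Protocol article*

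**What the plan says.** All references are to the protocol article.

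- **Unit of randomisation.** The Abstract (Methods) states: "Caregivers and their children are randomly assigned by village to intervention or control condition". The section on neighborhood selection, matching and randomization adds that "34 villages were matched into pairs based on various community, preschool and health service characteristics, and stratified by size and relative remoteness", and then: "In each pair, villages were then randomly assigned to the intervention group".
- **Place of delivery.** Study setting: "The intervention is delivered in informal preschools in rural villages in the district".
- **Model terms.** Data analysis plans: "Parent/child age and gender, allocation group, and baseline scores will be included as covariates". The next sentence adds the site term: "Analyses will also control for intervention site in order to account for variance in implementation among sites".
- **Model class.** The sentence after that specifies multilevel or random-effect models, "which can account for clustering of repeated assessments within individuals and clustering of individuals within villages".

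The article gives no definition of intervention site and does not say how the term enters the model.

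**The concern.** The site sentence comes after the covariate list, which already contains allocation, and before the sentence that introduces the village level. It therefore reads as a further adjustment, separate from the random village effect. If a site is where the sessions are held, no site contains both arms. A fixed adjustment for it then takes up the whole between-arm comparison.

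The stated purpose is a second difficulty. How well the sessions are implemented is determined after randomisation and is part of what the intervention delivers. Control villages do not receive the sessions, so nothing comparable exists there to adjust for. Adjusting the intention-to-treat comparison for it would remove part of the effect being estimated, or would have no meaning in one arm.

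The sentence applies to the efficacy models for both primary and secondary outcomes, so an analyst who followed it literally would meet the problem throughout.

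**Working it through.** **The plan's own figure.** The article gives no figure for this point. Its sample size reproduces and does not bear on it: 123 × [1 + (30 − 1) × 0.05] = 123 × 2.45 = 301.35, and 301.35 × 1.1² = 364.6, or 365 per group.

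**Inputs.** 34 villages in matched pairs give 34 / 2 = 17 pairs, with one village per arm in each (neighborhood selection section). Allocation is a model term (Data analysis plans). The ICC is 0.05 and the design effect size is 0.30 (Power calculation).

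**What site could mean.** Delivery is in village preschools. The Supervision section uses the word for visits to intervention teams during delivery. The Discussion uses it for the whole study area, which takes a single value and cannot vary among sites. The groupings that hold or could hold both arms have other names (pairs, phases, geographic clusters of communities for the outreach days). Village or preschool is therefore the most natural reading, but it is an inference.

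**Rank of the fixed-effects part for each reading.** Allocation takes one value per village, so it equals the sum of the indicators for the intervention villages. Adding age, gender or baseline score does not remove that dependence.

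| Reading of site | Columns | Rank | Allocation identifiable? |
|---|---|---|---|
| Village, fixed: intercept + allocation + 33 indicators | 35 | 34 | No |
| Intervention villages only, controls as reference: intercept + allocation + 17 indicators | 19 | 18 | No |
| Matched pair: intercept + allocation + 16 indicators | 18 | 18 | Yes |
| Phase (assuming both arms in each): intercept + allocation + 1 indicator | 3 | 3 | Yes |
| Area holding both arms (6 areas assumed): intercept + allocation + 5 indicators | 7 | 7 | Yes |

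Fixed preschool indicators nested in villages fail in the same way as village indicators, because those in intervention villages still sum to allocation.

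**Village as a random intercept.** This was checked in 200 simulated trials with 34 villages, ICC 0.05 and a true effect of 0.300. Village size was assumed to be 22 children, close to 2 × 365 / 34 = 21.5. The mean estimate was 0.301, the mean standard error 0.104 and the empirical SD of the estimates 0.109. Allocation is estimable under this reading, and the site term adds nothing to the village level.

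**The case against.** The strongest reply is that nothing in the article says fixed effects or indicators. The next sentence specifies random-effect models with villages as a level, and the section also says that clustering will be accounted for throughout. Read together, control for site may simply be the village random effect, under which allocation is estimable. Site might also mean a grouping that spans both arms, such as the outreach-day locations. Coding is commonly left to a statistical analysis plan, an independent statistical team will do the analysis, and exact collinearity usually shows when a model is fitted.

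Much of this stands. A reader might infer that the treatment effect cannot be estimated under the plan as written. The article does not support that, because site is neither defined nor called fixed.

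A reader might also infer that the reported effect would become an arbitrary contrast of single villages. At the plan's ICC, two villages differ by chance with an SD of √(2 × 0.05) = 0.32, against a design effect size of 0.30. That follows only if fixed village indicators are entered and software then drops a column. Under the second coding in the table, dropping a site indicator compares one intervention village with 17 control villages, and the SD is √(0.05 × (1 + 1/17)) = 0.23. Neither figure is the expected consequence of the planned multilevel analysis.

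The reply does not rescue the sentence. If site is the random village effect, the sentence is redundant. If it is a grouping across both arms, the article does not say so. Neither reading makes implementation a suitable adjustment for an intention-to-treat comparison. This is also a stated instruction, not a detail left for later.

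**Conclusion.** The concern holds in a conditional form. The site sentence is an undefined instruction that should not stand on any reading the article supports. As a fixed village or preschool covariate, it is exactly collinear with allocation (rank deficiency of 1: 35 columns, rank 34, or 19 columns, rank 18). As a random village effect, it duplicates the level already specified and does no harm to the estimate. In both cases its purpose, adjusting for implementation, concerns a post-randomisation feature absent from control villages.

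The rank result is exact and rests only on villages being the randomised units. That site means village or preschool is inferred from where delivery takes place. The simulation rests on the assumed 22 children per village. No numerical bias can be attached to the planned analysis. The wording should be corrected before the models are fitted.

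**What to change.** Replace the site sentence with a statement on these lines:

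1. Village enters every efficacy model as a random intercept.
2. Beyond the listed individual covariates, fixed adjustment is limited to factors set before randomisation that span both arms: the matched pair or the size/remoteness stratum used in the randomisation. Phase may be added if each phase contains both arms, which the article should state.
3. Variation in implementation is examined within the intervention arm only, in the dose, process and moderator analyses that the article already plans.

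The second item also brings the analysis into line with the matched design, which the current covariate list does not mention.

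The cost is one sentence, with no change to data collection. If pair is fitted as a fixed factor, between-cluster degrees of freedom fall from 34 − 2 = 32 to 34 − 17 − 1 = 16. Adjusting for the broader size/remoteness strata would normally use fewer.
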